# Physical exercise and cognitive engagement outcomes for mild neurocognitive disorder: a group-randomized pilot trial

**DOI:** 10.1186/s13063-018-2865-3

**Published:** 2018-10-19

**Keywords:** Mild cognitive impairment, Neurocognitive disorder, Behavioral interventions, Cognitive training, Yoga

## Abstract

**Background:**

Amnestic mild cognitive impairment (aMCI) is considered a risk state for the development of dementia due to Alzheimer’s disease. It is also a period in which interventions may be most effective in slowing progression to dementia. Computerized cognitive training and increased physical activity have shown to be among the most promising interventions. However, current evidence from randomized controlled trials comparing cognitive training, physical activity, and an active control is inconsistent. Furthermore, the neural mechanisms underlying these interventions are currently unclear.

**Methods:**

The objective of the current pilot study is to explore the feasibility of a trial investigating the impact of computerized cognitive training, yoga, and an active control intervention (wellness education) in individuals with aMCI by conducting a group-randomized, multisite, parallel, three-arm pilot study. We will establish preliminary effect sizes regarding the association of each intervention with neuroimaging and cognitive and participant-reported measures. We also aim to estimate the strength of association between the various outcomes. The current trial aims to recruit 75 people with aMCI and their 75 cognitively healthy care partners through clinics and senior care facilities. The initial intervention will last 10 days and will consist of 1 h daily of the assigned intervention i.e., (yoga, computerized cognitive training, or wellness education) combined with 1 h of memory compensation training and 1 h of support groups. Twenty-five participants will be group-randomized to each arm using a random number generator. Study staff and participants will be kept blind until recruitment is complete for each group. After the initial two-week intervention, participants will continue the assigned intervention for 24 weeks. Outcome measures are: functional connectivity and cerebral perfusion as assessed by magnetic resonance imaging; cognition; daily functioning; mood; anxiety; self-efficacy; caregiver burden; quality of life; and study feasibility including recruitment and retention rates.

**Discussion:**

This pilot trial aims to investigate the feasibility of a trial studying the impact of computerized cognitive training, yoga, and an active control intervention in persons with aMCI on MRI-based functional connectivity and cerebral perfusion as well as cognition, daily functioning, mood, anxiety, and quality of life and feasibility?

**Trial registrations:**

ClinicalTrials.gov, NCT03095170. Registered on 23 March 2017.

**Electronic supplementary material:**

The online version of this article (10.1186/s13063-018-2865-3) contains supplementary material, which is available to authorized users.

## Background

Mild cognitive impairment (MCI) is often considered a risk state, or even a prodromal stage, for the development of dementia. MCI is characterized by the following criteria: (1) a cognitive concern; (2) cognitive impairment as measured by psychometric tests; (3) overall intact activities of daily living (ADLs); and (4) not meeting criteria for dementia [1]. In the Diagnostic and Statistical Manual of Mental Disorders, 5th Edition, the concept of MCI is named “Minor Neurocognitive Disorder” [2]. Delaying the progression to dementia in patients with MCI would drastically impact the economic burden of dementia [3] as well as the quality of life of patients with MCI and their families. For these reasons, there has been increasing interest in interventions and rehabilitation programs that target MCI.

The National Academy of Medicine brought together a committee of experts on Preventing Dementia and Cognitive Impairment to objectively document an evidence-based consensus on dementia and cognitive impairment research. Their findings, reported in *Preventing Cognitive Decline and Dementia: A Way Forward* [4], indicated that cognitive training and increased physical activity are promising interventions to prevent, delay, or slow MCI or clinical Alzheimer’s-type dementia. However, the current evidence from randomized controlled trials is insufficient. To improve future research and obtain more evidence on these interventions, they suggested methodological improvements such as using biomarkers and having an appropriate control group. They also indicated that most studies, thus far, have focused on individual interventions while a multi-modal model may be more beneficial.

The current trial, called Physical Exercise And Cognitive Engagement Outcomes for Mild Neurocognitive Disorder (PEACEOFMND), aims to incorporate these methodological suggestions. The PEACEOFMND trial will investigate the impact of computerized cognitive training versus yoga versus an active control group (wellness education) on functional connectivity and cerebral perfusion in the brain as well as on cognitive functions (working memory, attention, and global cognitive functioning), daily functioning, mood, anxiety, self-efficacy, caregiver burden, and quality of life. Associated with these behavioral interventions will also be assessed. To create a multi-component program, each experimental arm is combined with support groups and memory compensation training (MCT). Individuals with MCI and caregivers that participate in group therapy show greater acceptance of the MCI diagnoses than wait-list controls [5]. Memory compensation training was developed for individuals with *amnestic* MCI (aMCI) and involves training the use of a portable calendar and note-taking [6]. Individuals with MCI that are compliant in MCT are found to have a higher sense of memory-related self-efficacy and functional ability [7]. Other multicomponent intervention trials have shown to improve or maintain cognitive functioning [8]. Still, the neuroimaging correlates associated with these program elements have not been investigated thus far.

With regards to computerized cognitive training, the primary neuroplasticity changes have been observed by the use of functional MRI (fMRI) [9, 10]. Previous research has found that computerized cognitive training improvements in problem solving and reasoning were related to changes in occipitotemporal white matter integrity and functional connectivity between the superior parietal cortex and the inferior temporal lobe [9, 10]. It is believed that computerized cognitive training may help stabilize, recover, or compensate for loss of functional and structural brain connectivity due to the ongoing pathological processes in aMCI.

Physical exercise has also been suggested as a promising intervention to reduce cognitive decline in older adults at risk for dementia [11]. Physical exercise as a part of a multi-component intervention has shown to slow cognitive decline [8] and is associated with higher gray matter volume in MCI [12]. There is currently insufficient evidence to determine the most beneficial type of exercise for decelerating the rate of cognitive decline and dementia [4]. Yoga incorporates aerobic effects, strength, flexibility, and balance. Aerobic physical exercise is thought to improve cerebral perfusion mechanisms [13–15]. Aerobic exercise [16, 17] and flexibility, toning, and balance training [17] have also shown to impact functional connectivity in older adults and MCI.

The design of the current trial is a group-randomized, multisite, parallel, three-arm trial that seeks to compare the impact of the following interventions: (1) computerized cognitive training; (2) yoga; and (3) an active control (wellness education).

### Trial objectives and hypotheses

The primary aims of this pilot are:

#### Aim 1

To conduct a preliminary examination of the impact of computerized cognitive training, yoga, and an active control intervention (wellness education) on changes in cerebral perfusion and functional connectivity, as measured by magnetic resonance imaging (MRI) in people with aMCI. Specifically, we aim to:**1A:** Estimate effect sizes for changes in cerebral perfusion and functional connectivity in the different treatment groups. We hypothesize that there will be preliminary evidence for improved functional connectivity in the computerized cognitive training group compared to the other two groups and that there will be changes in the cerebral perfusion as a result of yoga.**1B:** Estimate the relationships between changes in cerebral perfusion and functional connectivity, cognitive function, daily function, mood, anxiety, and quality of life within the two experimental groups compared to the control group. We hypothesize that improvement in cerebral perfusion and functional connectivity will be associated with improvement in cognitive functions, daily function, mood, anxiety, and quality of life in the individuals with MCI. Furthermore, we hypothesize that these changes are associated with an improvement in mood, anxiety, quality of life, and caregiver burden.**1C:** Establish recruitment and retention rates for this trial design.

##### Power and sample size

In our analyses of the imaging measures over the six-month intervention period, we expect that treatments will reduce age-dependent changes, measured as percent reduction in change from baseline, i.e., effect size (Cohen’s d). Using pilot data, we calculated means and standard deviations (SD) of changes in imaging variables as estimates for the non-treatment group. As in Aim 1, roughly 120 participants per group would be needed to detect an effect size of 0.325 with 80% power and α = 0.05. These effect sizes correspond to reductions in age-related imaging changes of roughly 30% or 50%. The present trial will also allow us to begin building towards those trial sizes.

#### Aim 2

To estimate effect sizes regarding the impact of computerized cognitive training, yoga, or an active control (wellness education) delivered in a multicomponent program that provides memory compensation and support groups to all subjects on cognitive function, daily function, mood, anxiety, and quality of life in persons with aMCI. We hypothesize that cognitive function, daily function, mood, anxiety, and quality of life will be higher in the computerized cognitive training and the yoga groups than in the active control group.

##### Power and sample size

Meta-analysis of studies of cognitive impact in healthy older adults suggest Cohen’s d within groups was 0.325 for aerobic exercise and 0.327 for cognitive training [18]. A power analysis in Gpower assuming two independent means indicated 118 people per arm are necessary to have 80% power to detect this magnitude of a difference between samples. Due to the group-randomized nature of the current trial, it is possible that a higher n is required. The scope of this pilot funding opportunity limits us to just 25 aMCI patients and their 25 partners per arm, leading to a total of 75 aMCI patients and their 75 partners. The results of the current trial may serve as pilot data for future studies.

## Methods

### Setting

Potential trial participants will be recruited from the Memory Disorder Clinics, behavioral neurology and neuropsychology practices at the University of Florida, Mayo Clinic Jacksonville, and Tallahassee Memorial Hospital. There will be three program sessions at each site. In order to reach target sample size, the trial will be advertised in healthcare and elderly living communities, at information sessions in the community, as well as by local healthcare professionals. We will also utilize advertising via brochures, flyers, newspaper articles, or other means suggested through the University of Florida, Mayo Clinic Jacksonville, and Tallahassee Memorial Hospital as appropriate. Medical providers may also refer patients with aMCI to the program.

### Participants

Our target is to have a total of 75 couples, recruited approximately evenly across the three sites. Enrollment will happen in dyads (i.e., a person with aMCI and a healthy study partner). Twenty-five dyads will be assigned to each treatment arm. Once written informed consent is obtained, participants will be screened for their eligibility over the phone. The Clinical Dementia Rating scale (CDR) [19] will be used to confirm the aMCI status of the patient and the Telephone Interview for Cognitive Status for Memory (TICS-M) will be used to confirm study partners are cognitively healthy. Specific inclusion and exclusion criteria are outlined in Table 1.

**Table 1 Tab1:** Inclusion and exclusion criteria

Inclusion criteria	Exclusion criteria
For the person with aMCI: 1. Written informed consent for participation. 2. A formal diagnosis of amnestic mild cognitive impairment [1] (single domain or multidomain) in the last 6 months (by neuropsychological evaluation) OR A CDR score of 0 or 0.5 and a TICS-M score of at least 25 on the TICS-M. 3. Aged at least 50 years. 4. Either not taking or stable on nootropic(s) and/or pain medication on a dose and frequency that affects cognitive abilities for at least 3 months. 5. Fluent in English. For the study partner: 6. Written informed consent for participation. 7. Aged at least 21 years. 8. A score of at least 32 on the TICS-M 9. Study partner has at least twice-weekly contact with the participant.	For the person with aMCI: 1. MRI contraindications (e.g. ferrous metal in the body, claustrophobia, pregnancy) For both the person with aMCI patient and study partner: 2. Physical impairments, language comprehension deficits, or significant hearing disturbances that would limit ability to perform tasks or participate in the intervention

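### The no-diagnosis route into the aMCI group requires no impairment, so a person who meets the protocol's own mark for cognitive health can enrol as the aMCI participant

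*Protocol article*

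**What the plan says.** In Methods, Participants, inclusion criterion 2 of Table 1 gives two alternative ways to qualify as the person with aMCI. The first is a formal diagnosis by neuropsychological evaluation within the last six months. The second needs no diagnosis: "A CDR score of 0 or 0.5 and a TICS-M score of at least 25 on the TICS-M".

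The text above the table says that the CDR "will be used to confirm the aMCI status of the patient" and that the TICS-M "will be used to confirm study partners are cognitively healthy". The partner criterion in Table 1 is "A score of at least 32 on the TICS-M".

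The Background lists what characterises MCI. The list includes a cognitive concern and "cognitive impairment as measured by psychometric tests".

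Under Setting, recruitment starts from memory clinics and specialist practices, and "the trial will be advertised in healthcare and elderly living communities, at information sessions in the community".

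**The concern.** An eligibility rule for an impaired population has to do two things: keep out people who are too impaired, and establish that some impairment is present. The second route does only the first. It accepts any TICS-M score from 25 upwards and treats CDR 0 and CDR 0.5 alike, so nothing in it separates aMCI from normal cognition.

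The pilot exists to supply numbers for a later trial in aMCI: effect sizes for imaging (Aim 1A) and for cognitive and participant-reported outcomes (Aim 2), associations between imaging change and the other outcomes (Aim 1B), and recruitment and retention rates (Aim 1C). All of these are meant to describe people with aMCI. If part of the group is not impaired, they describe a mixture whose composition the later trial may not share.

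**Working it through.** The document states no figure to reproduce here. The check is whether the rules, read together, can admit someone whom the protocol itself counts as healthy.

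**Step 1: the two TICS-M rules side by side** (both from Participants and Table 1)

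| TICS-M score | aMCI, second route (CDR 0 or 0.5 also needed) | Study partner |
|---|---|---|
| below 25 | fails | fails |
| 25 to 31 | passes | fails |
| 32 or more | passes | passes; taken as confirming cognitive health |

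Because 32 > 25, every score that certifies a healthy partner also meets the TICS-M condition for the aMCI participant. Only 25 to 31 separates the two roles.

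**Step 2: does the CDR condition close the gap?** No. CDR 0 and CDR 0.5 both pass. A person with CDR 0 and TICS-M 36 meets criterion 2 as the aMCI participant and also meets the partner's cognitive criterion. The overlap follows from the TICS-M rules alone and does not depend on any outside interpretation of CDR 0.

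**Step 3: does another criterion close it?** No. The remaining inclusion criteria for this person concern consent, age, stable medication and language. The only exclusion specific to this person is MRI contraindication. The shared exclusion covers physical, language-comprehension and hearing limitations. None requires a cognitive concern or a low test score.

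**Step 4: compare with the Background.** The MCI definition there requires a cognitive concern and impairment on psychometric testing. The second route requires neither. The statement that the CDR confirms aMCI also fails on this route, since both permitted values lead to the same decision.

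**Step 5: effect on the recruitment rate.** Let f be the share of enrolled 'aMCI' participants who are not impaired. The document gives no value for f. The true aMCI rate is (1 − f) times the observed rate, so the overstatement relative to the true rate is f/(1 − f). For assumed values of f:

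- 10%: 0.10/0.90 = 11%
- 20%: 0.20/0.80 = 25%
- 30%: 0.30/0.70 = 43%

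These show how the error scales. They are not estimates for this trial.

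**The case against.** **The heading presupposes aMCI.** The criteria stand under a heading for the person with aMCI, and the text speaks of dyads containing such a person, so the intent is clear. That is so, but criterion 2 is the only working definition beneath the heading, and a heading cannot supply a test that the criterion leaves out.

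**It may be a slip, or a bound lost in condensing.** This is plausible and cannot be settled from the article. It does not remove the point: Table 1 is presented as the specific criteria, and the rule it states is inconsistent with its neighbours. This is a wrong rule, not a missing detail.

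**The second route may hardly be used.** Memory clinics and specialist practices are named as sources, providers may refer patients with aMCI, and people who respond to community advertising may already hold a diagnosis. This stands. The document supports saying that unimpaired people can enrol, not that they will.

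**The comparison between arms is not biased.** Patients and staff stay blind to a session's allocation until its recruitment is complete, so loose entry is not tied to arm. This also stands, apart from chance imbalance with three sessions per arm. The problem is whom the estimates describe.

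**A person with genuine amnestic impairment could score 32 or more.** The document offers 32 only as a partner threshold and does not show that it is the right upper limit for aMCI. This stands and limits how firmly a cut-off can be proposed.

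**Conclusion.** The point holds as a contradiction within the protocol. As written, the second route can place a person with CDR 0 and a TICS-M of 32 or more in the aMCI group, although the same section treats that TICS-M score as confirming cognitive health. The conclusion rests only on the stated criteria and the Background's definition. Its practical size is unknown, because the document gives no enrolment by route.

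Three stronger readings are not supported:

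- **Dilution of the planned effect.** A reader might scale d = 0.325 down by the unimpaired share and inflate the required sample size. That assumes no benefit in unimpaired people, yet the power section for Aim 2 takes 0.325 from a meta-analysis in healthy older adults. No dilution of that figure follows. The pilot's 25 dyads per arm are in any case set by funding.
- **Ceiling effects on the DRS-2, FAQ and E-Cog.** The article gives no score distributions from which to show them.
- **Certain use of the route in the community.** Advertising there makes it possible, not established.

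**What to change.** Reconcile the second route with the Background's MCI definition so that it requires evidence of impairment. One form that uses the protocol's own figures is an upper TICS-M bound consistent with the partner cut-off of 32, with CDR 0 not sufficient unless there is a formal diagnosis. The sponsor should confirm the cut-off, because the document does not establish 32 as the right limit for this purpose. The sentence on what the CDR confirms should be aligned with the result.

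For dyads already enrolled:

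1. Record whether entry was by formal diagnosis or by the second route.
2. Among second-route entrants only, flag those with CDR 0 or a TICS-M of 32 or more.
3. Repeat the main estimates and the recruitment rate without the flagged dyads, and report both sets.

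The flag should not extend to formally diagnosed patients. They qualify by diagnosis whatever their CDR or TICS-M, and Table 1 does not require a TICS-M of them.

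The cost is an eligibility amendment, which is still feasible because Trial status reports recruitment as ongoing at submission, and somewhat slower recruitment. The sensitivity analysis needs no new data, since the second route cannot be applied without both scores.

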### Randomization and blinding

The group nature of intervention allows participants to compare their experiences, so individualized randomization poses a risk for diffusion of treatment effects. However, the group format limits in the ability to randomize per couple. Thus, we will block randomize by group instead of by participant assuring equal randomization of sessions to each of the three arms of the trial at each site. In other words, everyone in the first intervention period will receive the same treatment determined at random. The next intervention group will receive one of the two remaining arms also determined at random. The study biostatistician will randomize using a computerized random number generator to determine initial and second sessions at each site. The biostatistician is not involved in recruitment, assessment, or intervention delivery in any way. Due to the nature of the intervention, participants cannot be blinded. However, to mitigate selection bias, patients as well as study staff will be kept blind until recruitment for each session has been completed. Sessions will be offered sequentially three times in year 1 and include 6–12 individuals with aMCI and study partner couples per session. Hence, there will be the opportunity to block randomize nine (three sites × 3) sessions involving approximately 25 couples per arm for a total of 75 participants. A flow chart diagram showing summary of the pilot trial design can be found in Fig. 1.

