
### Intervention timeline

There will be nine different intervention groups, each starting at a different point in time. The initial intervention period will consist of 1 h daily of the assigned intervention (yoga, computerized cognitive training, or wellness education) in combination with 1 h of memory compensation training and 1 h of support groups. This will last for a period of ten days, delivered weekdays over two weeks. After the initial two-week intervention, participants will continue the intervention they were assigned to (yoga or computerized brain fitness) for another 24 weeks. Participants need to engage in the assigned intervention for at least 2 h for at least 20 out of 24 weeks to be considered a program completer. They are encouraged to do more. Attendance of the weekly yoga session as well as the number of minutes spent on yoga at home will be recorded each week. Individuals who miss a yoga session will be called by the study staff with the goals to record the number of minutes spent on yoga at home and will be encouraged to attend the next yoga session. For the computerized cognitive training arm, staff will track progress solely through the BrainHQ™ portal on a weekly basis. Individuals who spend < 120 min on computerized cognitive training will be contacted by the study staff and will be encouraged to spend more time on computerized cognitive training next week. The wellness education group will be asked to fill out and submit wellness logs for sleep, nutrition, and mood each week for 24 weeks. Individuals who do not send in their weekly log will be contacted via phone by the study staff and will be encouraged to send in their log next week. The amount of phone calls of the study coordinators to the participants will be recorded. Participants will not be restricted in concomitant care and interventions. A timeline chart from the perspective of participants is shown in Fig. 2.

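### Arm order is drawn site by site with nothing to balance it across sites, so arms will probably be unbalanced over first, second and third session; a 3×3 Latin square would prevent this with the same nine sessions

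*Protocol article*

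**What the plan says.** Under Randomization and blinding, the protocol article makes the session the unit of allocation and blocks by site, so that every site runs each arm once. The draw has two steps. In the first, "everyone in the first intervention period will receive the same treatment determined at random". In the second, "The next intervention group will receive one of the two remaining arms also determined at random". The third session takes whichever arm is left. The draw is described at site level: "The study biostatistician will randomize using a computerized random number generator to determine initial and second sessions at each site".

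The Setting section gives the number of sessions: "There will be three program sessions at each site". On timing, the randomisation section says "Sessions will be offered sequentially three times in year 1", and Intervention timeline adds "There will be nine different intervention groups, each starting at a different point in time". The randomisation section also keeps patients and staff blind to a session's arm until recruitment for that session is complete.

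Statistical methods describes linear mixed models for change from baseline to about six months. No constraint on arm order across sites is stated anywhere in the article.

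**The concern.** Arm is crossed with site by design but not with session position. Position can matter when sessions follow one another through a year: therapists and staff gain experience, the recruitment pool changes, and the baseline and six-month visits fall at different times of year. Three sites are too few for chance to even this out.

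Aims 1A and 2 estimate effect sizes for imaging, cognition, daily function, mood, anxiety and quality of life, and the hypotheses compare arms. The article expects the results to serve as pilot data for future studies. If one arm tends to come early and another late, a trend over sessions in the six-month change becomes part of the estimated difference between them. The allocation decides whether that can be separated later, so an analysis plan can repair it only in part.

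**Working it through.** **Inputs.** From Setting and Randomization and blinding: 3 sites, 3 sessions per site, 3 arms, each arm once per site, 6 to 12 couples per session, about 25 couples per arm and 75 in all. Independence of the three site orders is inferred from the site-level wording and the absence of any cross-site rule.

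**The plan's own figures.** The article describes "block randomize nine (three sites × 3) sessions involving approximately 25 couples per arm for a total of 75 participants". 3 × 3 = 9 sessions. 75/9 = 8.33 couples per session, within 6 to 12. 3 × 8.33 = 25 couples per arm. These agree.

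**Number of allocations.** Each site has 3! = 6 orders, so there are 6³ = 216 equally likely sets.

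**Balanced allocations.** There are 12 Latin squares of order 3. P(balanced) = 12/216 = 5.6%, so P(unbalanced) = 204/216 = 94.4%.

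**Size of the imbalance for a given pair of arms.** Within a site the position difference is ±1 in 4 of 6 orders and ±2 in 2 of 6. Its mean square is (4×1 + 2×4)/6 = 2. Averaged over three independent sites this is 2/3, and √(2/3) = 0.82 sessions. By enumeration the absolute difference in mean position is 1 in 28 draws, 1.33 in 24, 1.67 in 12 and 2 in 2. That makes 66/216 = 30.6% at 1 session or more. The extreme of 2 sessions occurs in 2/216 = 0.9%.

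**Can order be adjusted for afterwards?** The model is site + order + arm on the nine session means.
- A given arm is in a given position at all three sites in 216 × (1/3)³ = 8 draws. Over 9 arm-position pairs that is 72. The 6 draws with identical order at every site are counted three times each, so the number of distinct draws is 72 − 12 = 60 (27.8%).
- In 54 of these 60, exactly one arm is aliased with its position, and the contrast between the other two arms is still estimable. In the other 6, all three contrasts are lost.
- A given contrast is lost when either of its arms is aliased: 54 × 2/3 + 6 = 42, and 42/216 = 19.4%.
- With order as a single linear term, a given contrast is lost only when all sites share one order: 6/216 = 2.8%.

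**Precision in the remaining draws (categorical order).** All contrasts are estimable in 216 − 60 = 156 draws. The average contrast variance, in units of the session-mean variance, is:

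| Draws | Average variance | Ratio to Latin square |
|---|---|---|
| 12 (Latin) | 0.667 | 1.00 |
| 108 | 0.933 | 1.40 |
| 36 | 1.000 | 1.50 |

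**Possible bias.** The documents give no drift size. Assume a linear drift in six-month change of 0.1 to 0.2 SD per session. RMS bias in an unadjusted contrast = 0.816 × 0.1 = 0.08 SD, to 0.816 × 0.2 = 0.16 SD. Against the reference effect of 0.325 under Aim 2, that is 0.082/0.325 = 25% to 0.163/0.325 = 50%. Both figures scale directly with the assumed drift.

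**The case against.** The strongest reply is that nothing here is an error. The plan describes a proper restricted randomisation, drawn by a biostatistician who has no part in recruitment, assessment or delivery, and a pilot need not add a second blocking factor. That is right as far as it goes, and the point is an improvement to the design. A condensed article may also omit a cross-site constraint that the full protocol contains, which is why independence is given above as an inference.

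Four stronger readings are tempting, and the documents do not support them.

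- *Any trend over the year biases the contrasts.* The analysis is of change from baseline. A shift in recruitment mix or level that affects both visits equally cancels; only a trend in the six-month change matters.
- *In 27.8% of draws arm and order cannot be separated.* That is the share in which at least one arm is aliased. For a given contrast the figure is 19.4%, or 2.8% if the trend is linear.
- *A Latin square removes season.* The nine groups start at different times, so the same session number need not fall in the same season at each site. Season is balanced only so far as it does.
- *Order bias becomes exactly zero.* This requires an order effect common to all sites and equally weighted sessions, and sessions may hold 6 to 12 couples.

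The objection with most force concerns concealment. A Latin square makes the sites' sequences dependent. With staggered starts, knowing the first arm at two sites reveals the first arm at the third, and one site's full order leaves only two possible squares. Delivered arms cannot be hidden, because participants are not blinded. This is a real cost. It is limited because an arm is disclosed only after that session's recruitment closes, the sites are separate institutions, and each site's third session can already be deduced under the present plan.

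**Conclusion.** The point holds as a cheap improvement to a valid design. If site orders are drawn independently, imbalance over session position is close to certain (94.4%), and for a given pair of arms it is a full session or more in 30.6% of draws. Adjusting afterwards may fail for a given contrast (19.4% with categorical order, 2.8% with a linear term). In the non-Latin draws where every contrast survives, it costs 40 to 50% in average variance compared with a Latin square.

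How much harm follows depends on a session-order trend in six-month change, which the documents do not quantify. The 0.08 to 0.16 SD range illustrates an assumed drift and is not an estimate of what will happen. A reader might infer that the planned randomisation is biased; it is not, since the expected imbalance over repeated draws is zero. The risk lies in having one realisation with three sessions per arm.

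**What to change.** Have the biostatistician draw one of the 12 Latin squares of order 3 at random, with sites as rows, session order as columns and arms as cells. Each arm then runs once at each site and once in each position. The nine sessions and about 25 couples per arm are unchanged, and the chance of imbalance over session order falls from 94.4% to 0. If the full protocol already contains such a constraint, the article should say so.

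Trial status reports that recruitment is ongoing, so some sessions may already have run. In that case, draw at random among the remaining sequences that best balance order. Either way, report results by session order or adjust for it.

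The text change is about one sentence, with no extra participants, sessions or staff. The cost is the cross-site predictability described above. Limit it by holding sequences centrally, not sharing delivered arms between sites, aligning session starts where feasible (which also improves the balance over season), and keeping each allocation concealed until that session's recruitment closes.
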